## Abstract

**Background:**

Bronchiolitis is a common lung infection that affects infants and young children. While most children can be treated at home, some require hospitalisation where supportive care, such as fluids and oxygen, is the suggested treatment. Bronchiolitis is the leading cause of infant hospitalisation in developed countries and exerts a significant burden on the healthcare system. The aim of the Bronchiolitis in Infants Placebo Versus Epinephrine and Dexamethasone (BIPED) study is to evaluate the effects of a combination of epinephrine and dexamethasone, given during initial presentation at the emergency department, on hospitalisation for bronchiolitis. This article outlines the statistical analysis plan (SAP) for the BIPED study.

The BIPED study is a Phase III, multi-centre, randomised, controlled, double-blinded superiority, placebo-controlled trial to determine whether the combination of epinephrine and dexamethasone is successful in reducing hospitalisation for bronchiolitis up to 7 days following presentation at an emergency department with bronchiolitis. The secondary outcomes include hospital admissions for bronchiolitis at the emergency department enrolment visit, and all-cause hospital admissions, health care provider visits and health care-related costs in the 21 days following enrolment. The safety outcomes are gastrointestinal bleeding, serious bacterial infection, severe varicella and death.

**Discussion:**

The BIPED study will provide evidence on whether a combination of epinephrine and dexamethasone reduces hospitalisation in infants following presentation to the emergency department with bronchiolitis. These data will be analyzed using this SAP, submitted before the data became available for analysis, to reduce the risk of bias in our reported outcomes.

**Trial registration:**

ClinicalTrials.gov NCT03567473. Registered on June 25, 2018.

## Background

Bronchiolitis exerts substantial pressure on healthcare systems in developed countries, both in terms of health-related expenditure and hospitalisation, and is the primary cause of hospitalisations in infants [1–4]. Despite this burden and significant research expenditure, there is no evidence on an effective treatment for bronchiolitis [5]. International guidelines recommend only supportive care, including the administration of fluids and oxygen as necessary [6]. However, a large multicenter trial indicated that a combination of nebulised epinephrine and oral dexamethasone could potentially reduce hospitalisations for children with bronchiolitis, compared to placebo [7]. Furthermore, international guidelines have called for research to determine whether this combination therapy is an effective treatment for bronchiolitis [6, 8, 9]. The Bronchiolitis in Infants Placebo Versus Epinephrine and Dexamethasone (BIPED) study aims to collect this evidence.

The BIPED study is a phase III, multi-centre, randomised, controlled, double-blinded, superiority placebo-controlled trial that will investigate the combination of two treatments of inhaled epinephrine and two doses of oral dexamethasone as a treatment for bronchiolitis. The BIPED study will enrol infants who present at the emergency department (ED) with bronchiolitis. The study protocol has been published separately [10]. This article outlines the final statistical analysis plan (SAP) for the BIPED study. This SAP has been published before completing the data lock for the BIPED study and aims to reduce bias in the final trial report.

### Objectives

The primary aim of the BIPED study is to determine whether infants with bronchiolitis treated with inhaled epinephrine in the ED and a two-day course of oral dexamethasone will have fewer hospitalisations related to bronchiolitis over the 7 days following ED presentation, compared to infants treated with placebo. We will enrol infants aged between 60 days and 12 months who present at the ED with bronchiolitis during the period deemed to be the season for respiratory syncytial virus (RSV) bronchiolitis. The secondary objectives are to investigate the effect of the combination of epinephrine and dexamethasone on hospital admission for bronchiolitis at the enrolment ED visit, all-cause hospital admissions at 21 days, and health care provider visits (including ED visits) and health care-related costs within 21 days post-enrollment in the trial. The primary outcome will also be investigated in the participants who present at the ED with their first episode of bronchiolitis.

## Method/Design

### Design and setting

The BIPED study is a phase III study conducted in 12 sites across Canada, Australia and New Zealand. All participating hospitals are members of the Pediatric Emergency Research Canada (PERC) network [11] or the Paediatric Research in Emergency Departments International Collaboration (PREDICT) [12], both of which are affiliated with the Pediatric Emergency Research Networks (PERN). The BIPED study will define bronchiolitis as an episode of wheezing or crackles in an infant aged between 60 days and 12 months, alongside signs of an upper respiratory tract infection during the period deemed to be the season for RSV bronchiolitis. To reflect international clinical guidelines and practice, we have not restricted our definition of bronchiolitis to the first episode of wheezing or crackles and will enrol infants with second and subsequent episodes of bronchiolitis, with each infant only enrolled once into the study.

The active treatment in the BIPED study is two treatments of epinephrine (either via nebulisation (3 mg) or via metered dose inhaler and spacer (MDI-s) (625 mcg)) given 30 min apart in the ED and two doses of once daily oral dexamethasone (0.6 mg/kg per dose, up to a maximum of 10 mg), known as EpiDex. The first dose of dexamethasone will be given immediately before the first dose of epinephrine, and the second dose will be given 24 h later. The BIPED study will compare EpiDex to a placebo control (oral dexamethasone vehicle and nebulised normal saline or an inert placebo by MDI-s) by randomising participants in a 1:1 ratio. All study personnel, bedside clinicians, and participants/caregivers are blinded to the study group assignment. Participants will be followed up for 21 days following their ED enrolment visit, with the primary outcome collected at 7 days (168 h) post enrolment.

### Study protocol development and conduct

The BIPED study was registered on ClinicalTrials.gov on June 25, 2018, registration number NCT03567473. The BIPED study protocol received approval from Health Canada and local research ethics boards (REB) at each site prior to commencing enrolment. Informed consent will be obtained from all legal guardians before administering the study interventions. The BIPED study is being undertaken within the Canadian KidsCAN-PERC iPCT network [13] and the Australian-New Zealand PREDICT network. The data management and trial oversight, including safety, is being undertaken by the KidsCan-PERC iPCT trials network through a centralised structure and independent data and safety monitoring board (DSMB).

### Randomisation and data collection

Eligible participants will be randomised using permuted-block randomisation, stratified by site. This randomisation strategy ensures that differences in standard practice across sites will be equally represented in each study group. Additionally, block randomisation ensures that seasonal variation in the response to therapy will be comparable across the two groups. The statistician performing providing the randomisation lists is not involved in the study in another capacity.

Study participant research data will be stored using the REDCap electronic data capture system [14], based at a secure data coordination centre (DCC) at the Women and Children’s Health Research Institute (WCHRI), University of Alberta [15]. Individual participants will be identified with a unique study identification number.

### Primary outcome

The primary outcome is admission to hospital for bronchiolitis within 7 days (168 h) of study enrolment. BIPED study defines hospitalisation as any of the following conditions:The participant is admitted to an inpatient ward.An ED length of stay of 12 h or greater.A combined ED and observation unit length of stay of 12 h or greater.

ED length of stay at enrollment visit is defined as the time between the administration of first study medication (or time of consent when no study medications are received) and discharge from the ED or observation unit. The length of stay for all return ED visits will be measured from time of triage or registration, whichever is sooner.

### Secondary outcomes

#### Efficacy outcomes

The BIPED study will include four secondary outcomes:Admission to hospital for bronchiolitis at enrolment ED visit.All-cause hospital admission within 21 days following enrollment ED visit.All-cause health care provider visits (including ED visits) within 21 days following enrollment ED visit.Health care-related costs within 21 days of enrollment following enrollment ED visit.

#### Safety outcomes

The safety of the EpiDex combination will be assessed with the following outcomes:Gastrointestinal bleeding (involving melena or frank blood per rectum not attributed to other causes by the treating physician).Serious bacterial infection (defined as meningitis, osteomyelitis or septicaemia).Severe varicella (defined in the protocol [10]).Death.

#### Exploratory outcomes

The BIPED study will collect 10 additional exploratory outcomes:Admission to hospital for bronchiolitis within 21 days following enrollment ED visit.Intensive care unit (ICU) admissions within 21 days following enrollment ED visit for bronchiolitis and requiring intubation or continuous positive airway pressure (CPAP).All cause hospital admission within 7 days following enrollment ED visit.All cause ED visits within 21 days of enrollment ED visit.Length of stay (in hours) for the enrollment ED visit for participants who are discharged at the enrollment ED visit.Length of hospital admission (in hours) for participants admitted at their enrollment visit.Resolution of symptoms as documented on a standardised questionnaire during the telephone or email at day 7 and 21 days.Out of pocket expenses borne by the family/caregiver in the 21 days following enrollment ED visit.Health care utilisation for respiratory illness up to 18 years of ageDevelopment of respiratory illnesses such as asthma and recurrent wheezing up to 18 years of age.

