#### Exploratory outcomes

Exploratory outcomes (a)–(d) will be analysed using relative risk regression and report the posterior mean absolute-risk difference and relative risk with corresponding 95% credible intervals. Exploratory outcomes (e) and (f) are uncensored time-to-event outcomes and will be analysed as a Bayesian Cox proportional hazards model fit with the Integrated Nested Laplace Approximation [28] method in R [29], adjusted for site. We will report median hazard ratios and their corresponding 95% credible intervals.

Exploratory outcome (g) is a repeatedly measured binary outcome and will be analysed using a hierarchical Bayesian relative risk regression to adjust for patients. From this model, we will report mean relative risks alongside 95% credible intervals. Exploratory outcome (h) will initially be analysed using a Bayesian linear model to report the mean difference in expenses alongside a 95% credible interval. Graphical methods will be used to assess normality of residuals, and a lognormal or gamma model will be fit, if required. Exploratory outcomes (i) and (j) will not be analysed at the primary trial analysis of the trial. Thus, a separate analysis plan will be developed before the completion of the 18-year follow-up period.

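### The two length-of-stay comparisons, exploratory outcomes (e) and (f), are made within groups that EpiDex is meant to change, so a drug that averts milder admissions can appear to prolong stay

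*SAP article*

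**What the plan says.** In the SAP article, the exploratory outcomes listed under Method/Design include, as fifth and sixth items, "Length of stay (in hours) for the enrollment ED visit for participants who are discharged at the enrollment ED visit" and "Length of hospital admission (in hours) for participants admitted at their enrollment visit". The section Exploratory outcomes under Analysis for secondary endpoints calls these (e) and (f). It says that they "are uncensored time-to-event outcomes and will be analysed as a Bayesian Cox proportional hazards model", fitted by the Integrated Nested Laplace Approximation "method in R [29], adjusted for site. We will report median hazard ratios and their corresponding 95% credible intervals".

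The event that sorts infants into the two groups appears elsewhere as an efficacy outcome. The first secondary outcome is "Admission to hospital for bronchiolitis at enrolment ED visit". The Objectives state the trial's hypothesis that treated infants "will have fewer hospitalisations related to bronchiolitis over the 7 days following ED presentation".

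The Primary outcome section also counts as hospitalisation "An ED length of stay of 12 h or greater". It starts the enrolment-visit clock at first study medication, or at consent if none was given.

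The article plans no length-of-stay analysis in all randomised infants, no severity adjustment for (e) and (f), and no caveat about how the two groups are formed.

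**The concern.** Randomisation makes the arms comparable at entry. It does not make the admitted infants of one arm comparable with the admitted infants of the other once treatment has influenced who is admitted.

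Suppose EpiDex keeps some milder infants out of hospital. Its admitted group then loses its mildest members, so the average severity of those who remain rises. Its discharged group gains infants who are sicker than the rest of that group. If sicker infants stay longer, both groups look slower to leave on EpiDex. A drug that does what the trial hopes could therefore show unfavourable hazard ratios in both analyses at once, and site adjustment does nothing about it.

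The 12-hour rule may add to this. If that definition of hospitalisation also governs (e) and (f), which the article does not say, the duration being measured helps to decide which group an infant falls in.

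At stake is how two reported hazard ratios are read. A reader could not tell a treatment effect on stay from a change in who was counted.

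**Working it through.** The plan states no length-of-stay figure to reproduce. The check asks what (e) and (f) would show if EpiDex changed admission and nothing else.

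**Inputs from the SAP article**
- Placebo hospitalisation probability 0.35 and target difference 8 points (Statistical principals), so 0.35 − 0.08 = 0.27 on EpiDex. The primary outcome is counted over 7 days; using these rates for the enrolment visit is an assumption.
- 410 evaluable infants per arm (Sample size calculation). The inflation for 5% loss reproduces: 410/0.95 = 431.6, rounded up to 432 per arm, 864 in total.

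**Step 1: shift in composition.** If EpiDex only averts admissions and causes none:
- 8/35 = 22.9% of the placebo admitted group has no counterpart in the EpiDex admitted group.
- 8/73 = 11.0% of the EpiDex discharged group would have been admitted on placebo.

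**Step 2: simulated hazard ratios.** Everything in this model beyond the inputs above is assumed.
- Severity s is standard normal. An infant is admitted when s exceeds the cut-off giving 35% (placebo) or 27% (EpiDex), so the averted admissions are the least severe ones.
- Stay depends on u = ρs + √(1 − ρ²)·e, with e independent standard normal noise.
- Hospital stay is exp(ln 48 + 0.7u) hours; ED stay is exp(ln 4 + 0.5u) hours.
- Treatment has no effect on any infant's own stay.
- A Cox model for discharge is fitted within each group, without site effects or priors. A hazard ratio below 1 means a longer stay on EpiDex.

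Hazard ratios come from 400,000 infants per arm. The last two columns come from 2,000 trials of 410 per arm and give the share in which the 95% interval lies wholly below 1 (nominal 2.5%).

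| ρ | HR (f) admitted | HR (e) discharged | Interval below 1, (f) | Interval below 1, (e) |
|---|---|---|---|---|
| 0 | 1.00 | 1.00 | 3.1% | 3.3% |
| 0.3 | 0.96 | 0.97 | 5.8% | 5.8% |
| 0.5 | 0.93 | 0.94 | 9.8% | 10.6% |
| 0.7 | 0.89 | 0.90 | 15.4% | 22.5% |
| 0.9 | 0.83 | 0.84 | 29.0% | 55.7% |

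With 35% admission in both arms and ρ = 0.5, the hazard ratios are 1.00 for both outcomes to two decimals (1.001 and 0.995). Both conditions are therefore needed: an effect on admission and a link between severity and stay.

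**Step 3: size in hours at ρ = 0.5.** The median in (f) goes from 69.6 to 73.6 h, a shift of 4.0 h. In (e) it goes from 3.48 to 3.58 h, a shift of 0.10 h or 6 minutes.

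**Step 4: a true shortening of stay at ρ = 0.5.** A real shortening of about 5% is hidden in (f) (HR 0.99) but visible in (e) (HR 1.04). A real shortening of about 10% shows in both (HR 1.06 and 1.15).

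**Step 5: all randomised infants.** Mean hospital hours, counting 0 for infants not admitted, are 26.6 on placebo and 21.0 on EpiDex at ρ = 0.3, 29.9 and 24.4 at ρ = 0.5, and 33.3 and 27.6 at ρ = 0.7. The reversal disappears.

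**The case against.** Several points on the other side stand.

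- **The bias is conditional.** A reader might infer that (e) and (f) are biased whatever happens. That is not supported: with no effect on enrolment-visit admission, or no severity-stay link, the hazard ratio is about 1.00. The direction in (f) also needs the averted admissions to be the milder ones. If they were a random sample of admissions, the severity mix in (f) would not change.
- **The size is assumed.** The article gives no stay durations, no severity-stay correlation and no admission rate specific to the enrolment visit. It is easy to pick stays for averted and remaining admissions that yield a difference of many hours, but the article supports no such single figure. The hard severity cut-off in the simulation also separates averted from remaining admissions more cleanly than practice would.
- **The reach is limited.** These are two of ten exploratory outcomes. The 99% superiority rule is framed for primary and secondary outcomes, and only hazard ratios with intervals are planned here. Admission effects are reported separately through the primary outcome, secondary outcomes one and two, and exploratory outcomes (a) and (c).
- **Two wider inferences fail.** A reader might suppose that enrolment-visit admissions make up most of the primary outcome, but the article does not give the split. A reader might also fear distorted cost results, but costs have their own economic analysis and nothing says they will be derived from these hazard ratios.
- **Dropping (e) and (f) would go too far.** They are prespecified, and recruitment and follow-up have ended. A single Cox model for all infants also mixes ED discharges within hours with much longer ward stays, so proportional hazards is doubtful.

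None of this removes the structural problem. The groups are defined by an outcome that treatment is intended to alter, and the plan attaches between-arm hazard ratios to them without warning.

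**Conclusion.** The concern holds as a conditional one. If EpiDex averts milder admissions at the enrolment visit and severity is related to stay, both hazard ratios lean towards a longer stay on EpiDex with no infant's stay lengthened. The first condition is close to what the trial hopes to show.

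Under the assumed 35% versus 27% admission and correlations of 0.3 to 0.9, the spurious hazard ratio runs from about 0.96 to 0.83 for (f) and from 0.97 to 0.84 for (e). These ranges illustrate the mechanism and do not predict the trial's result. A real shortening of stay that is large enough would still show.

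The matter is worth correcting but moderate to minor. It concerns exploratory outcomes only and leaves the primary conclusion untouched.

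**What to change.** Before the data lock, which Trial status anticipates by the end of September 2025:

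1. Add one analysis in all randomised infants with data: time from first study medication (or consent if none was given, the clock already set in the Primary outcome section) to discharge home from the enrolment episode, whether from the ED, observation unit or ward, adjusted for site.
2. Check proportional hazards in that analysis. If it fails, report a difference in mean or restricted mean hours instead of a hazard ratio.
3. Keep (e) and (f), but report them descriptively by arm, without hazard ratios, and state that the two subsets are not randomised comparisons.

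The cost is a change of wording and a little extra analysis, since (e) and (f) already call for the discharge times. The addition comes after recruitment and follow-up ended, so it must be labelled as a late one.

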### Sample size calculation

The sample size was determined using the average length criterion (ALC) [16], a Bayesian method for sample size determination. Using the ALC, we chose the smallest sample size for which the average length of the 95% high-density posterior credible interval for the difference in admission rates between placebo and EpiDex is below 9%. We determined the average length of the posterior credible interval across the prior-predictive distribution for the data [16]
. To determine the relevant prior distribution, we performed an expert elicitation for the probability of hospitalisation under placebo and EpiDex [17]. We simulated 1500 studies from the prior-predictive distribution and computed the posterior distribution for the absolute difference using 5000 simulations to estimate the average length of the 95% posterior credible intervals. Based on this simulation, the sample size of 410 participants per arm for the BIPED study was selected [17]. We allowed for a 5% loss to follow up, leading to a total target recruitment of 864 participants, 432 per arm.

### Interim analysis and stopping guidance

There are no planned interim analyses of efficacy outcomes. The DSMB will review all safety outcomes at least once a year for the duration of the study. The DSMB, alongside the trial steering committee, will consider stopping for safety concerns.

## Statistical analysis plan

### Statistical principals

Outcomes will be collected with a standardised survey issued to parents/caregivers either over email or by telephone 7 and 21 days after enrollment in the BIPED study. Non-responders will be sent a second email and, if necessary, up to six attempted phone calls over 3 days. Once 21 days have elapsed following enrolment, the participant’s medical record will be reviewed to track any return ED visits, hospital admissions and additional healthcare contact. Admissions and ED visits reported by caregivers to study hospitals must be confirmed on medical record review. Similarly, at the six study hospitals where admissions and ED visits to non-study hospitals can be confirmed by administrative database review, non-study hospital ED visits and admissions reported on the survey will be confirmed. For study sites where visits and admissions to non-study hospitals cannot be confirmed by administrative database review, the caregiver’s report of and reason for these visits/admissions will be used to determine whether the participant met the study definition of admission. The final trial analysis will take place after every participant has reached 21 days after enrolment and all the data have been collected and cleaned. The analysis will be performed in a blinded manner.

The final trial analysis will use a Bayesian inferential framework based on the posterior probability that the EpiDex combination is superior to placebo for the primary and secondary outcomes. It will follow the intention-to-treat principle. The EpiDex combination will be declared superior to placebo if the posterior probability of superiority is above 99%, with simulations confirming a type 1 error rate of 4.1% with a probability of hospitalisation equal to 0.35 and a power of 81% with a target difference of 8%. Due to the likelihood principle, corrections for multiple comparisons will not be used. All estimates for the treatment effect will be reported using 95% high density posterior credible intervals, calculated using R [18] interfacing with Bayesian software such as JAGS, stan or INLA [19–21].

